## 5 STUDY POPULATION

*Leave blank. Text should be included under the relevant subheadings below.*

### 5.1 INCLUSION CRITERIA

This study targets active SYHealth patients with diabetes mellitus (DM) who have not had a retinal exam in the last 11 months. The study will recruit and randomize a cohort of 848 adults (424 per arm) from SYHealth-Chula Vista and SYHealth-King-Chavez clinic sites. In order to be eligible to participate in this study, an individual must meet all of the following criteria:

1. Provision of signed and dated informed consent form.
2. Stated willingness to comply with all study procedures and availability for the duration of the study.
3. Established and active patient of SYHealth-CV and KC (having a medical appointment in the last 18 months).
4. Person aged 22 and older.
5. Established diagnosis of DM.
6. Medical appointment(s) (in-person or telehealth) scheduled during the intervention period.
7. Has not completed a dilated eye exam or retinal exam in the last 11 months.
8. Be able to read, understand, and speak English or Spanish at a level sufficient to consent to participation, comprehend educational materials and sessions, and complete surveys.

### 5.2 EXCLUSION CRITERIA

The study will exclude individuals who present any of the following conditions, as there is no benefit to screening or insufficient data to prove safety and/or benefit (e.g., pregnancy). Additionally, selected criteria align with EyeArt® contraindications based on the FDA clearance.

1. Prior diagnosis of eye problems including retinopathy, blocked blood vessels, macular edema, or retinal vascular occlusion.
2. Persistent visual impairment in one or both eyes.
3. History of ocular injections, laser treatment of the retina, or intraocular surgery (excluding cataract surgery).
4. Individuals with contraindication for fundus photography (for example, have symptomatic light hypersensitivity).
5. Pregnant women.
6. Diagnosis of mental or degenerative disease that prevents self-consent for the study.

### 5.3 LIFESTYLE CONSIDERATIONS

For the DRES-POCAI study, no lifestyle considerations will be part of the eligibility screening process.

### 5.4 SCREEN FAILURES

The eligibility screening will be completed before consenting potential participants and randomization (**Study schema 1.2**). For individuals who do not meet the eligibility criteria or are unable to participate in the DRES-POCAI research study, the study staff will express gratitude for their time and interest in the study. Individuals will be given contact information to schedule their routine retinal screening appointments (SYHealth's Quality department). Additionally, the staff will provide handouts about diabetes and eye health to encourage these individuals to maintain their diabetes care and management with their SYHealth primary care provider.

The study does not anticipate screen failures as defined as "participants who are consented to participate in the clinical trial, who do not meet one or more criteria required for participation".

## 6 STUDY INTERVENTION

### 6.1 STUDY INTERVENTION(S) ADMINISTRATION

*Leave Blank. Text should be included under the relevant subheadings below.*

#### 6.1.1 STUDY INTERVENTION DESCRIPTION

The purpose of the DRES-POCAI research study is to improve eye care by using a special camera and a computer system called EyeArt® to make diabetic eye screenings faster and more accessible. Eligible participants that choose to participate will complete a survey about diabetes management and eye health. They will also be randomized and assigned to one of the two study groups: usual care (receive a retinal screening by an eye care provider) or intervention group (receive a retinal screening using a special camera and EyeArt®). The study visit (baseline) is expected to be completed in a period of ~60 minutes.

During the first study visit, participants will:

1. Complete informed consent
2. Fill out a survey on diabetes, eye health, and barriers to retinal screening completion.
3. Undergo randomization and be assigned to a study group: usual care or intervention.
4. Undergo DR Screening. *Intervention group* participants will complete the DR screening using a special camera and the artificial intelligence (AI) system (EyeArt®) on the same day of the study

visit. Participants will also complete a satisfaction survey related to the use of EyeArt system to complete their DR screening.

*\*\*Usual care group* participants will complete the DR screening with an eye care provider on a different day and at a different location. The study staff will assist in scheduling appointments for the DR screening to ensure the completion of this important component.

5. Health Education Overview and Engagement materials: at the end of the study visit, the study staff will provide participants with an overview of the health education sessions. Staff will also ensure participants have scheduled any/all follow-ups. Participants will receive educational materials about diabetes care and management, eye health, etc.

Complete medical visit: Participants will complete a medical visit on the same day as the study visit (for in-person visits). If the medical visit is via telehealth, then participants will complete it on a different day after the screening.

Follow up contact with participants: After the first (baseline) study visit, all participants will participate in one 20-minute educational session and complete a short survey within 6 months of the baseline. Upon the completion of the second health education session and the 6-month follow-up survey, participants will receive a \$25 gift card.

For participants in the intervention group who had a negative initial DR screening, they will be asked to complete their follow-up DR screening one year after the initial enrollment.

Both arms will be encouraged to follow up with their eye care provider for comprehensive eye exams.

---

## 6.1.2 DOSING AND ADMINISTRATION

**Not applicable**

---

## 5.2 PREPARATION/HANDLING/STORAGE/ACCOUNTABILITY

---

### 5.2.1 ACQUISITION AND ACCOUNTABILITY

**Not applicable**

---

### 5.2.2 FORMULATION, APPEARANCE, PACKAGING, AND LABELING

**Not applicable**

---

### 5.2.3 PRODUCT STORAGE AND STABILITY

**Not applicable**

---

### 5.2.4 PREPARATION

**Not applicable**

---

## 6.3 MEASURES TO MINIMIZE BIAS: RANDOMIZATION AND BLINDING

To minimize study intervention bias and variability, the study is using a randomized controlled, open-label, parallel superiority trial. By randomizing, research participants have an equal opportunity of being

selected into the intervention or control group of the study. Using a computer generated (randomizer application on a tablet or touchscreen device) random number assignments will be given. This process will help generate comparable groups, thereby minimizing the effects of variables other than the variable under evaluation. Randomization will allocate participants into either the Intervention group, which will utilize a Point-of-Care Topcon® non-mydratic retinal camera connected to the EyeArt® AI software for DR screening, or the control group, which will receive usual care screening, in a 1:1 ratio, respectively. This method aims to minimize bias and ensure that the differences observed between the two groups can be attributed to the intervention itself rather than other external factors.

The research study staff – Research Assistants (RA) will be responsible for the randomization process. The study team will implement strict procedures to ensure that the allocation sequence is conducted during the participant group assignment with the RAs. No allocation will be determined before a participant arrives. This process will prevent selection bias and ensures that study personnel cannot influence group assignment based on participant characteristics or interest. The RAs will press a designated button on the application to initiate the random assignment, the assigned group will display clearly on the screen for the participant to either the intervention group or the control group.

To mitigate the bias due to the lack of blindness, objective outcomes such as DR screening rates and referrals, as well as validated patient surveys regarding knowledge and self-efficacy, will be used. Furthermore, the research team will implement strict measures to minimize open-label bias. This includes:

- a) Establishing standardized procedures for data collection, assessment, and outcome measurement to mitigate the influence of bias on study results. This ensures consistency and reliability across all study groups.
- b) Implementing robust data monitoring processes overseen by the Data Safety and Monitoring Committee (DSMC) to safeguard the integrity and validity of study findings.
- c) Employing statistical methods to adjust for potential biases, such as sensitivity analysis to address differences between treatment groups. These measures collectively strengthen the reliability and credibility of the study outcomes.

Regarding control group expectations, participants in the usual care group may be less motivated to seek external eye exams knowing the immediate screening results are not available during the study. The study will emphasize the importance of comprehensive eye exams in both groups to mitigate this. In addition, both usual care and intervention groups will receive health education materials and care coordination support, this is anticipated to increase engagement for participants in the usual care group.

By implementing these measures, the study team will minimize bias in randomization and enhance the validity and reliability of study results, addressing the absence of blinding.

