| Study Description: | This study is intended to address unmet medical needs in diabetic eye care in a community health center setting by enhancing and modifying existing clinical practices with the integration of point-of-care (POC) artificial intelligence (AI) technology for Diabetic Retinopathy (DR) screening. The study will optimize, implement, and test the impact of a multicomponent intervention that includes: 1) autonomous DR screening, a fast and non-invasive retinal exam into the primary care settings with 2) integration of the results into the EHR and 3) health education/care coordination support (e.g., patient education).                                                                                                                     |
| Objectives:        | 
Primary Objective (Clinical): Evaluate the implementation and effectiveness of a multicomponent AI clinical intervention on DR screenings rate, early stages of DR detection, and referrals to the specialist for follow up on abnormal results.
 
Secondary Objectives: Evaluate the implementation and effectiveness of a multicomponent AI clinical intervention on DR knowledge, attitudes, self-efficacy, and patient satisfaction.
                                                                                                                                                                                                                                                                                           |
| Endpoints:         | 
Primary Endpoint (Clinical): DR screening status, stages of DR detection, and referrals to the specialist for follow up on abnormal results.
 
Secondary Endpoints: DR patient engagement, intention to engage in future DR screenings.
                                                                                                                                                                                                                                                                                                                                                                                                                                                                                            |

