| Evaluate the implementation and effectiveness of a multicomponent AI clinical intervention on DR screenings, early stages of DR detection, and referrals to the specialist for follow up on abnormal results. | 
 
1. Completion of DR screening. Data will be obtained through EHR at the time of the enrollment (baseline).
 
2. Results of the DR screening: for usual care specific diagnosis; for intervention group defined as normal, mild-to-moderate DR (mtmDR), visual threatening DR (vtDR) or ungradable. Data will be obtained through EHR at the time of the enrollment (baseline) and over the duration of the study.
 
3. Referral to specialist completion status and final diagnosis. Data will be obtained through EHR over the duration of the study.
 
 | 
To evaluate the effectiveness of the clinical intervention will be tested using a RCT (Aim 2), with the “intervention group”, which is characterized by 1) conducting autonomous DR screening system (H2.1) with 2) integration of the results into the EHR (H2.2). The “usual care” group represents the existing primary care model, which involves medical visits, referral to the specialist for a DR screening, and follow-up.
 
In addition, to evaluating the impact and efficiency of the POC-AI System we will also collect AI system data, number of orders submitted, screenings completed (images), number of ungradable and time of attempts, time the patient spent in front of the camera.
 |

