## 4.2 SCIENTIFIC RATIONALE FOR STUDY DESIGN

The DRES-POCAI study is using a randomized controlled, open-label, parallel superiority trial. The benefit of this trial is that each participant will be randomized to two intervention options, allowing researchers to compare the relative effectiveness of multiple intervention options. The DRES-POCAI study employs a randomized controlled, open-label, parallel superiority trial design. This design is well-suited to achieve the study's aims for several reasons:

**Randomization:** Random assignment of participants to intervention and control groups minimizes confounding variables. This ensures that any observed differences in outcomes are likely due to the intervention itself and not pre-existing differences between the groups. Participants of the DRES-POCAI study will be randomized into two groups: usual care (receive a retinal screening by an optometrist) or intervention group (receive a retinal screening using a special camera and EyeArt® system, *an autonomous AI-based DR screening*). The randomization will occur after consenting and completing the surveys, prior to conducting the DR screening process (for those randomized to the intervention group).

**Open-label Design:** The open-label nature is appropriate given the practical realities of implementing a multi-component intervention with integrated technology. Blinding participants and providers to the autonomous DR screening is logistically difficult. The intervention's immediate results and potential impact on the workflow necessitate an open-label approach.

**Parallel Design:** The parallel design allows for a clear, side-by-side comparison of outcomes between the intervention and usual care groups over time. This establishes the efficacy of the multicomponent approach. Also, this approach streamlines research analysis and clearly compares outcomes within the defined study period.

**Superiority Evaluation:** The primary objective is to determine if the multi-component DRES-POCAI intervention is superior to usual care in increasing DR screenings, early detection, referrals, and patient knowledge/self-efficacy. A superiority trial directly establishes whether the intervention offers significant benefits over the current model.

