#### 4.3 JUSTIFICATION FOR DOSE

**Not applicable**

#### 4.4 END OF STUDY DEFINITION

The end of the study is defined as the completion of the last study-related activity at the close of the 2-year study. Participants of the DRES-POCAI study are considered to have completed the study if they have completed all the phases of the study, including the last scheduled DR screening shown in the **Schedule of Activities (SoA), Section 1.3**. A DRES-POCAI participant's individual study period will be considered complete upon the occurrence of the following, whichever comes latest:

**Completion of Baseline Visit:** During the first study visit, participants will complete consent, fill out a brief survey about diabetes care and eye health. At this time, the participant will also be randomized and assigned to the usual care or intervention group.

**Completion of Diabetic Retinopathy Screening:** The intervention group will complete the DR screening using a special camera and the AI system (EyeArt®), the same day of the study visit. The usual care group will complete the DR screening with an eye care provider on a different day and at a different location. The study staff will facilitate this process for participants in the usual care group by assisting them in scheduling appointments for their routine retinal screening. The study staff will provide an overview of the health education sessions, provide engagement and educational materials and schedule the follow-up health education visits with all participants. This step will ensure the completion of this important component.

**Participant Satisfaction Survey (Intervention Group Only):** Participants will complete the end-of-study satisfaction survey.

**Medical visit:** Both study groups will complete a medical visit after the screening. If the medical visit is in-person, then participants will complete it the same day as the screening. If the medical visit is via telehealth, then participants will complete it on a different day after the screening.

**Completion of Health Education Program:** Attendance at all scheduled health education sessions (3 sessions within the 6 months after the study visit) along with completion of any associated post-program evaluation surveys.

**One-Year Follow-Up Screening (Intervention Group Only):** Participants who had a negative initial DR screening will complete a follow-up screening one year after their initial enrollment and the participant satisfaction survey.

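### The protocol claims that a three-part package is superior to existing usual care, but the education and support part goes to both arms, so the randomized contrast is the AI screening pathway alone

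*Combined protocol and SAP*

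**What the plan says.** **The tested intervention.** The protocol synopsis (1.1) lists three components: autonomous screening, then "integration of the results into the EHR and 3) health education/care coordination support". Section 2.3.3 again treats education and care coordination as part of the intervention. Section 4.2 makes it the primary objective to show that the multicomponent intervention is "superior to usual care in increasing DR screenings, early detection, referrals, and patient knowledge/self-efficacy". H2.3 (SAP, Study Design; protocol 4.1) predicts greater knowledge, attitudes, self-efficacy and satisfaction than in controls.

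**Who receives the third component.** Section 6.3 states that "both usual care and intervention groups will receive health education materials and care coordination support". Section 6.1.1 says that "all participants will participate in one 20-minute educational session". Section 4.4 has staff book education visits with every participant and help the usual-care arm "by assisting them in scheduling appointments for their routine retinal screening". Section 2.3.2 lists information and navigation support among the benefits that do not depend on group.

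**The comparator.** Section 3 describes the intervention group by the first two components only ("characterized by 1) conducting autonomous DR screening system (H2.1) with 2) integration of the results into the EHR (H2.2") and describes usual care as the existing primary care model. Section 6.3 expects the shared support to change behaviour in controls: "this is anticipated to increase engagement for participants in the usual care group".

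**The concern.** The stated contrast (three components against existing care) is not the contrast that randomization creates. A component given to both arms cannot explain a difference between them, and a comparator that receives study education and booking help is not simply the existing model.

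Two conclusions are at stake. A positive primary result could be reported as a gain of the multicomponent package over current practice, and a clinic would then misjudge what it needs to adopt and what it can expect. On H2.3, either a null or a positive result could be read as evidence about the education programme, although both arms are offered that programme.

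**Working it through.** **1. Components by arm, as the documents describe them.**

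| Component | Intervention arm | Usual-care arm |
|---|---|---|
| Point-of-care AI screening | Yes (6.1.1, 6.3) | No; exam by an eye care provider on another day and at another place (4.4, 6.1.1) |
| AI result opened in the EHR | Yes (1.1) | Not applicable; the optometrist documents the result (1.1) |
| Education sessions and materials | Yes | Yes (4.4, 6.1.1, 6.3) |
| Care coordination, navigation, booking help | Yes | Yes (2.3.2, 4.4, 6.1.1, 6.3) |
| Follow-up tied to the EyeArt result | Yes (2.2, 8.1) | No EyeArt result |
| Satisfaction survey | Yes (4.4, 8.1) | No |

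The first two rows and the follow-up row separate the arms. Education does not: no section sets out a programme that differs by arm. Sections 1.3 and 4.4 give three sessions, while 6.1.1 gives one and then mentions a second. That needs reconciling, but 4.4 and 6.1.1 each apply their count to all participants.

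**2. Consequence for H2.3.** The SAP plans a difference-in-differences analysis of the knowledge outcomes. Write the mean change as E + A in the intervention arm and E in controls, where E is the effect of shared education and A the effect of receiving the AI screen. The estimate is (E + A) − E = A, so E cancels whatever its size. This assumes that education works equally in both arms. For H2.3(d), with satisfaction surveyed in one arm, no between-arm difference can be formed.

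**3. The plan's sample size, reproduced.** Inputs (SAP, Sample Size): 59% v 69%, two-sided α 0.05, power 80%, 1:1, Pearson χ².

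n per arm = [z₀.₉₇₅√(2p̄q̄) + z₀.₈₀√(p₁q₁ + p₂q₂)]² / d², with p̄ = 0.64 and d = 0.10

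= [1.960 × √0.4608 + 0.842 × √0.4558]² / 0.01 = (1.3305 + 0.5682)² / 0.01 = 360.5, so 361 per arm and 722 in total. This matches the SAP.

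**4. Sensitivity to the control rate (illustration only).** The documents give no size for the effect of the shared support on screening. Power = Φ{[d√n − 1.960√(2p̄q̄)] / √(p₁q₁ + p₂q₂)}, with √361 = 19:

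| Control v intervention | Calculation | Power |
|---|---|---|
| 59% v 69% (plan) | (1.900 − 1.3305)/0.6751 = 0.844 | 80% |
| 62% v 69% (controls rise, intervention fixed) | (1.330 − 1.3176)/0.6704 = 0.018 | 51% |
| 62% v 72% (both rise by 3 points) | (1.900 − 1.3033)/0.6612 = 0.902 | 82% |
| 56% v 69% (controls lower, intervention fixed) | (2.470 − 1.3419)/0.6785 = 1.663 | 95% |

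At the enrolment target of 424 per arm, 62% v 69% gives 57%.

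**The case against.** The strongest reply is that the primary comparison is already about the tool. The SAP gives its purpose as the impact of the EyeArt system on screening completion, and section 6.3 randomizes between screening methods. Sharing education is open and deliberate: section 6.3 offers it because controls may be less motivated. Holding it constant to isolate the screening method is a legitimate design. All of this stands, and it is why the primary test is not in question. It does not remove the conflict, because the SAP's Study Design section still calls the intervention multicomponent and the comparator usual care, and retains H2.3.

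Three further inferences are tempting, and the documents do not support them.

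- *That the arms do not differ at all on the third component.* Clinical staff follow up according to the EyeArt result (2.2, 8.1), and educators explain the limits of AI screening (2.3.3). Coordination therefore differs in part.
- *That the control arm will exceed 59%, so the trial is underpowered.* Section 6.3 anticipates engagement and gives no rate. In the other direction, the synopsis reports 46% screening at these clinics, eligibility requires no retinal exam for 11 months (5.1), and the outcome window is 3 months (SAP) or 60 days (9.4.2). In 6.1.1 the AI screen comes before the education overview, so the support might act more on controls, but nothing gives its size. The net direction is unknown.
- *That H2.3 must come out null.* A same-day result discussed with a provider could still separate the arms. The SAP also treats knowledge outcomes as exploratory, and nowhere plans to conclude that education fails.

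**Conclusion.** The concern holds as a conflict between the stated claim and the design. The randomized contrast is point-of-care AI screening with EHR-integrated results, and follow-up tied to those results, against usual-care screening, with education and support in both arms. That comparison is valid for screening completion. The trial cannot attribute an effect to education, cannot claim that the three-component package beats existing usual care, and has no control data for satisfaction.

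The size is one of interpretation and not of a wrong number: 722 reproduces exactly. Power between 51% and 95% for control rates of 62% to 56% rests on my assumed 3-point shifts with the intervention fixed at 69%. It shows sensitivity and predicts nothing. The conclusion does not depend on it. It rests on reading sections 2.3.2, 4.4, 6.1.1 and 6.3 as describing what controls will receive.

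**What to change.** Leave conduct as it is and reconcile the wording in the SAP Study Design section and protocol sections 1.1, 2.3.3, 3, 4.1, 4.2 and 6.3.

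1. Name the comparator as usual care plus study education, materials and scheduling support. Name the tested contrast as point-of-care AI screening with EHR-integrated results.
2. Drop the superiority claim for the full package.
3. Recast H2.3(a)-(c) as the effect of receiving AI screening, and state that the result is not evidence for or against education.
4. Report H2.3(d) descriptively, for the intervention arm only.
5. State beside the sample size that 59% is historical and was not measured under the support given to controls, so the trial's control rate may be higher or lower. Label power at other rates as illustration.

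The cost is redrafting, with no change to visits, procedures or data. The downside is a claim narrower than the multicomponent description, but it is the claim that the design can support.
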